## **B. Significance**

Excellence in hand hygiene protects veterans from MRSA and other HAIs and is a major patient safety goal. In one study, a multifaceted hand hygiene intervention decreased HAIs by 42% and overall incidence of MRSA from 2.16 to 0.93 episodes per 10,000 patient days ( $p<0.001$ ). However, few evidence-based interventions for improving hand hygiene exist and none are included in the current VA Required Hand Hygiene Practices Directive (2011-007). In addition, the VA Office of Inspector General (OIG) recently issued a report entitled, *Evaluation of Prevention Practices in Veterans Health Administration Facilities (11-03361-274)*. In the report, OIG recommended that intervention strategies be initiated “when hand hygiene performance falls below established thresholds” as required by The Joint Commission. In response to OIG’s recommendation, the Office of the Deputy Under Secretary for Health for Operations and Management (DUSHOM) and the Office of the Deputy Under Secretary for Health for Policy and Services (DUSHPS), Office of Public Health requested that Drs. [name] and [name] design and analyze a VA-wide facility survey of hand hygiene practices. (See Preliminary Studies Section The same Offices also asked Drs. [name], [name], and [name] to complete a meta-analysis of hand hygiene interventions. (See Preliminary Studies Section The Under Secretary of Health stated in his response to the OIG report that the results of these studies would be used to inform a web-based hand hygiene toolkit maintained by the Office of Public Health, IDPIO. Findings from this proposed study will be directly disseminated through the hand hygiene toolkit. Drs. [name] and [name] will develop the materials for dissemination which will include the most effective hand hygiene signs, detailed information about the “bundled” intervention and its overall effect, and recommendations for tailoring and implementing the intervention based on the Aim 2. Thus, this project will lead to immediate impact by providing products for dissemination to improve quality of care.

The effort to improve hand hygiene practices continues to expand in VHA. Multiple VHA offices are coordinating efforts to establish a national hand hygiene initiative. Our study team is collaborating with several programs within the Offices of Public Health (COHIC, IDPIO) and Patient Care Services (IDPO) to reach this objective. The efforts include participation on the National Hand Hygiene Workgroup, chaired by [name] with [name] as a committee member, [name] chairing the Workgroup’s Hand Hygiene Intervention Subgroup, and a serving on the planning committee and presenting at the VA-wide Summit promoting hand hygiene practices.

In addition, [name], [name], and [name], all of whom are internationally-recognized experts in hand hygiene and infection control, have served as advisors in developing the hand hygiene bundle being tested in this study. They have graciously agreed to continue to serve on quarterly Advisory Board meetings over the duration of the study to review the progress of the project and to assist in implementation and dissemination decisions.

Finally, this proposal will benefit from an annual Implementation and Dissemination Advisory Committee that will include all mentioned operation partners, the Hand Hygiene Advisory Board members, and include two VHA implementation experts: [name], an implementation science expert and recent acting director of the Inpatient Evaluation Center, and [name] (Ann Arbor VAMC), an expert in the implementation of infection prevention interventions. [name], the Director of the Office of HAI Prevention Research and Evaluation of the Centers for Disease Control and Prevention (CDC)'s Division of Healthcare Quality Promotion (DHQP), will also join the Advisory Committee. [name] has been involved in advising VA's MRSA Initiative for over 5 years starting with Pittsburgh's pilot study and through the recent long-term care study in VA CLCs that determined that 58% of CLC residents are MRSA colonized. Our research team and the studies we are conducting are poised to shape VHA policy on improving hand hygiene compliance and decreasing MRSA and other HAIs among our veterans.

### 3.0 Objectives

The proposed study will use a parallel, mixed-methods design that will integrate qualitative research (Aim 2) with a cluster-randomized controlled trial (Aim 1).

**Specific Aims:** The two specific aims and associated hypotheses of the project include:

- 1) Identify combinations of hand hygiene intervention strategies that optimize hand hygiene compliance and that could form an evidence-based hand hygiene bundle for VHA implementation.

*Hypothesis 1: Combinations of interventions will increase compliance rates more than single interventions.*

*Aim 1* will entail a 30-month cluster-randomized controlled trial that will sequentially test three individual hand hygiene interventions to identify an optimal combination of interventions to increase hand hygiene compliance. The trial will be conducted in 59 hospital units in 10 VA hospitals in order to test the efficacy of individual and then sequentially added interventions to determine their incremental impact on hand hygiene compliance.

- 2) Identify institutional, organizational, ward/ICU, and individual level facilitators and barriers to implementing hand hygiene interventions.

*Hypothesis 2: Facilitators and barriers will pattern around contextual factors such as level of leadership support and organization of infection control programs.*

*Aim 2* will entail a qualitative process evaluation that includes site visits to purposefully selected sites, semi-structured interviews, and observations to examine barriers and facilitators to the interventions and develop contextual insight for implementing and scaling-up the intervention at additional sites as a national initiative.

#### 4.0 Resources and Personnel

The central site will be the Iowa City VA Health Care System. Research staff at Iowa City will be responsible for patient data pulled from VA administrative datasets and compiling and securely storing all hand hygiene observation data for Aim 1. Iowa City research staff will be the only staff performing Aim 2 (qualitative process evaluation). For Aim 2, the Iowa City research staff will recruit VA personnel to participate in individual and group semi-structured interviews. They will also be responsible for the informed consent protocol and conduct all of the interviews.

The nine other participating sites will contribute to efforts of Aim1 of the study. Each site will be in charge of 1) conducting observations of potential HCW hand hygiene opportunities (Site Research Coordinator), 2) hanging up the hand hygiene signs (Site PI/Hospital Epidemiologist), 3) working with the site's ICP to distribute individual hand sanitizers (Site PI/Hospital Epidemiologist), and 4) obtaining and displaying HCWs hand cultures (Site PI/Hospital Epidemiologist).

There will be 10 sites included in this study and they are detailed in section 5.1, which includes table 1, "Site Selection."

Data analysts at the Iowa City VA will perform analysis and be responsible for data management. Only Iowa City VA staff will have access to the data.

## 5.0 Study Procedures

### 5.1 Study Design

**Site Selection:** Table 1 lists the 10 VA hospitals participating in the study. The table also indicates whether the site is in VISN 23 and whether Aim 2 will be conducted at the site. The sites were carefully selected to represent geographical variation—covering the Northeast to Northwest and Midwestern, Southern, and Western states. In addition, the hospitals represent small, medium, and large facilities within VA. Finally, this study is embedded in a larger set of integrated studies as part of a CREATE application focused on combating MRSA and other HAIs. One of the broader aims of these studies is to develop a VISN-level computer model to assist leadership in policy decision-making around the spread of MRSA and other HAIs. Therefore, we selected all three tertiary care hospitals in VISN 23 to ensure we have a rich set of data for a single VISN. The 6 sites for Aim 2 were selected to balance the need for depth of data in a single VISN (Iowa City, Minneapolis, and Omaha), geographic variation (Baltimore, Portland, Miami, and VISN 23), and successful collaboration on previous projects (Baltimore, Iowa City, Portland). All general medicine and surgical wards and ICUs will participate in the study. (Psychiatric wards were excluded due to restrictions regarding alcohol-based hand sanitizer.)

**Table 1: Site Selection**

| Site              | Number of ICUs | Number of Wards | Total Number of Units/Wards | VISN 23 | Aim 2 |
|-------------------|----------------|-----------------|-----------------------------|---------|-------|
| Ann Arbor VA      | 2              | 4               | 6                           |         |       |
| Baltimore VA      | 3              | 2               | 5                           |         | X     |
| Boston VA         | 3              | 8               | 11                          |         |       |
| Iowa City VA      | 1              | 2               | 3                           | X       | X     |
| Miami VA          | 3              | 3               | 6                           |         | X     |
| Minneapolis VA    | 2              | 7               | 9                           | X       | X     |
| Omaha VA          | 1              | 2               | 3                           | X       | X     |
| Portland VA       | 1              | 2               | 3                           |         | X     |
| San Antonio VA    | 3              | 5               | 8                           |         |       |
| Salt Lake City VA | 2              | 3               | 5                           |         |       |
| Total             | 21             | 38              | 59                          |         |       |

**Aim 1** involves a sequential cluster-randomized controlled trial that will be conducted in 10 VA hospitals to evaluate the individual and combined impact of three approaches to improving hand hygiene compliance. The primary outcome measure will be directly observed hand hygiene. The unit of analysis will be hospital wards/ICUs.

**Outcome Measures:** Hand hygiene compliance is the primary outcome measure. Compliance rates will be determined using the same methods of direct observation of HCWs developed by [name] for his VA HSR&D funded study (IIR 09-099). (See Cluster Randomized Trials (CRT) in 2.A.) The secondary outcome measure is MRSA acquisition. Both compliance and MRSA infection rates will be collected monthly throughout the project for each of the 59 units.

*Operationalization of Primary Outcome:* Nurses, physicians and other staff will be observed for 10 consecutive minutes of clinical activity on the study wards and ICUs. Observers will be research staff specifically trained and validated in hand hygiene observations. (See Appendix for standardized observation worksheet.) The observation periods will be 10 minutes long so that observers can be transiently on the wards/units without their presence being noticed, which should minimize the Hawthorne effect. As [name] has done in his previous study, the observers will be given a "cover story" so that the true purpose of their observations will be hidden. Therefore, while observers will be on the wards, the HCWs will not know they are being watched for infection control purposes, so they will not artificially increase their compliance. In ICU settings, we will state that the observers are collecting data for a severity of illness aggregate measure, such as the APACHE score. In non-ICU, medical/surgical ward settings the observer will state that they are doing a patient movement and activity of daily living survey to determine the proportion of time patients who are isolated or non-isolated receive their trays of food or are transported outside of their rooms to physical therapy or radiology, etc. The standardized observation instructions and training protocol has been successfully implemented in other studies by the team. Hand hygiene opportunities at entry and exit of a patient's room will be recorded. We are using entry and exit because it is the one of the most common "hand hygiene opportunities" reported in the literature and by VA facilities. However, we will also record observations of the 5 Moments of Hand Hygiene as current hand hygiene observation guidelines recommend. Observations will occur during the day shift (75%) and night shift (25%). In addition, observations will include weekends (20%) and weekdays (80%).

*Operationalization of Secondary Outcome:* MRSA acquisition is defined as patients who are MRSA– and become MRSA+. MRSA acquisition will be analyzed as a rate looking at number of acquisitions per patient days per month on a ward/unit level basis. Healthcare-associated MRSA infections are collected by the VA Inpatient Evaluation Center (IPEC) and are defined according to guidelines of the CDC's National Healthcare Safety Network (NHSN). IPEC provides facility-level information about MRSA prevalence on a monthly basis. Since 2007, MRSA/MDRO coordinators at individual facilities have entered monthly data on surveillance testing and on the prevalence and acquisition of MRSA as well as the frequency of specific types of clinical MRSA infections including skin and soft tissue infections, urinary tract infections and central-line associated bloodstream infections into an SQL database maintained on a server at IPEC.

*Interventions:* Based on our systematic review, VA-wide survey, and our own pilot data we have identified the three interventions with the greatest likelihood of improving hand hygiene compliance and also in need of further study individually and in combination. The three interventions are: 1) theoretically-based and empirically-tested hand hygiene signs to serve as environmental cues to action and to reinforce of HCWs' perceptions of patient susceptibility, 2) personal hand sanitizers to decrease barriers and improve accessibility to hand sanitizer, and 3) HCW hand cultures to test the combination of individual feedback, environmental cues to action, and HCW perceptions of patient susceptibility and severity. This proposal will identify an optimal combination of interventions to increase and sustain hand hygiene compliance.

*Varying Environmental Cues to Action (Hand Hygiene Signs):* Hand hygiene signs and posters are one of the most common infection prevention interventions utilized in healthcare settings. Among VA hospitals, 97.2% report displaying hand hygiene signs in their facilities. Signs are also a low cost, easy to implement intervention. Furthermore, signs act as environmental cues to action, which the Health Belief Model suggests are important in triggering targeted behaviors or actions. However, signs are often quickly designed and taped up (e.g., “Foam In, Foam Out”) or printed off of a website promoting hand hygiene. They are rarely theoretically-based or empirically-tested. Recent evidence suggests that the content of signage affects the degree to which it prompts hand hygiene behavior; therefore, the specific message is an important component that needs to be considered. In preliminary studies, we have investigated the most effective theoretically-based messages to display on signs to improve HCW behavior. (See Preliminary Studies Section.) As discussed previously, gain-framed messages focused on helping patients appear to be most effective in changing HCW behavior. However, evidence also strongly suggests that repeated exposure to the same cues leads to a process of habituation such that their effectiveness at prompting behavior is diminished over time. Therefore, it is important to identify strategies for maintaining the salience of hand hygiene cues. One approach is to periodically modify the cues to increase their novelty and enhance the potential that HCWs will attend to and act on them. For the current proposal, we will study how to sustain their power as a cue to action by varying the frequency of changing the signs.

The specific signs that we will use in the proposed study will be based on those found to be most effective from our ongoing pilot work. We will use signs from the next phase of our pilot work in which we are testing multiple gain-framed, patient-focused signs with slight variations on message verbiage, color, and HCW and patient demographics. The six most effective signs will be changed at varying frequency depending on their randomization assignment. Although evidence suggests that periodically changing reminders is likely to reduce habituation and enhance their impact, little is known about the frequency at which this should occur. Therefore, signs will be changed at varying frequencies: every week, once a month, or displayed for the entire 6 months of this phase of the study, with effects on hand hygiene compliance compared across conditions. We will continue to use point-of-use to determine the placement of the signs. During the first site visits the qualitative team will document current practices surrounding the display of hand hygiene posters. They will also discuss how to best implement point-of-use signs with the infection control (IC) team at each site. We have worked with Baltimore VA, Iowa City VA, and Portland VA to create solutions to displaying signs next to dispensers on hospital units. For those sites at which we do not conduct site visits as part of Aim 2, we will conduct interviews over the phone to gather the necessary information. We will conduct the phone interviews after the site visits in ensure we will be able to integrate all necessary questions into the interview guide. The Site PI/Hospital Epidemiologist PI will be responsible for hanging the hand hygiene signs according to the protocol established for each site.

*Distribution of Individual Hand Sanitizer Gel to HCWs:* Easy access to hand hygiene products is known to improve hand hygiene compliance. The most common recommendation is to place alcohol-based hand rub dispensers at a patient's bedside. However, due to space configurations and fire codes, many hospitals are unable to implement this recommendation. To counter this barrier, some have recommended providing individual hand sanitizers to all healthcare workers. In the VA national survey led by members of our investigative team, 90.6% of VA hospitals reported that they provide staff with individual containers of hand sanitizer; however, the frequency of disbursement is inconsistent. Providing hand sanitizer to staff can also take a variety of forms from placing a jar of individual dispensers at a nursing station to making them available at a staff meeting. (Personal communication, [name], 11/10/11) During the site observations, we will document the current practices of the sites and

Figure 2. Image of Organisms Grown from HCW Handprint on a Blood Agar Culture Plate  
Courtesy of [name].

[figure not shown]

contact the four sites at which we are not conducting a qualitative evaluation to obtain information regarding current practices and how strategies for providing personal hand sanitizer may be improved to maximize usage.

Bottles of individual hand sanitizer will be distributed to HCWs at the intervention hospitals. The Site PI/Hospital Epidemiologist will coordinate distribution with the Nurse Managers and Medical Directors overseeing the units. The Research Coordinator will document how the hand sanitizers were distributed at each facility and provide the documentation to the Iowa City Research Coordinator. As part of our hand hygiene observation protocol, we will also document the source of the hand sanitizer that is used (e.g., individual hand sanitizer, wall dispenser at point of

care, etc.), as well as whether the individual hand sanitizer is visibly present on the HCW, to determine the extent to which this approach contributes to overall hand hygiene.

*Displaying HCWs' Hand Cultures:* Individualized feedback is an effective method of changing HCW behavior; however, it is a difficult strategy to implement when trying to improve hand hygiene compliance rates. Tracking hand hygiene compliance to an individual HCW through direct observation can be difficult because ideally the workers should be unaware they are being observed. Monitoring individual behavior without following a HCW's movement would be nearly impossible. Others have promoted automated hand hygiene monitoring systems as a means of tracking individual behavior without the barriers direct observation can pose. However, technical failures and lack of acceptance from staff impede the implementation of these systems.

An innovative approach is to display the hand cultures of HCWs. With this approach, HCWs are asked to place their hand on a blood agar plate in a large petri dish. The organisms left by the hand are then grown, a digital photograph is taken of the hand culture, and photographs of the cultures are displayed to provide feedback to the HCWs. (See Figure 2.) This combines the

effectiveness of individual feedback with environmental cues to action. Furthermore, direct visual evidence regarding the presence of pathogens on one's hands (and that of their colleagues) is likely to provide an especially salient affective or emotional source of motivation for improving hand hygiene (i.e., increases HCWs' sense of placing patients at risk).

For this intervention, the Site PI/Hospital Epidemiologist will be responsible for collecting blood agar culture plates of HCWs' hands on each unit once a month at the intervention hospitals. The Hospital Epidemiologist or a designated IC staff will go to each ward/unit and ask HCWs on the ward/unit at the time to place their hand on a blood agar plate. The HCW will be told the results (pictures of culture plates after organisms have been grown) will be confidentially displayed in staff work areas; however, if HCWs would like to their specific results, they can provide a four digit number that will be associated with their agar plate. We will not record their names or track the number. The number will be written on the culture plate and then on the digital photo for display. The research team will not record the number in any other way and will not record HCW names or any other identifying informations. HCWs will be responsible for their 4 digit number if they would like to find photo of their culture plate among the photos of culture plates from other HCWs. They will also be told the organisms left by their hands on the culture plates will not be identified (speciated), but any of the organisms grown on the culture plate could contribute to hospital-acquired infection in patients although likelihood varies by organism. Anyone on the ward/unit at the time will be eligible. HCWs will be able to opt out if they choose not to have their hand cultured. After organisms from HCWs hands are grown on the blood agar plates, a picture of the culture will be displayed in their unit with a four digit number attached (either provided by a HCW or randomly assigned). This will allow individual HCWs to confidentially view their own hands and the unit to see a general picture of the risk

Figure 3: Interventional Phases

[figure not shown]

they pose to their patients. Photographs of the hand cultures will be displayed in common staff areas, but out of patient view. During the initial site visits, the qualitative team will observe current feedback mechanisms on the wards and units and work with the IC team to plan a way of displaying the feedback. This information will be used in interviews and planning sessions conducted with the four sites the qualitative team does not visit. Since the collected of culture plates is an intervention and not being done for data collection purposes, all culture plates will be destroyed via proper disposal techniques and digital photographs of the culture plates will be used for educational purposes only.

Study Procedure: The trial will entail 6 phases. (See Figure 3.) As an overview, Phases 2, 4 and 6 will be intervention periods and Phases 3 and 5 will establish a new baseline and serve as washout periods. Importantly, Phase 2 randomization will occur at the ward/ICU level since our pilot data suggests room entry signs can be randomized at the ward/ICU level. However, to avoid crossover effects, the other interventions will be randomized at the hospital level in Phases 4 and 6.

Phase 1 will obtain baseline rates of hand hygiene compliance and MRSA on each unit at each hospital. Phase 2 will compare different strategies for changing hand hygiene signage on hospital units to determine if periodically varying signage more effectively modifies hand hygiene behavior than using static environmental cues. The 59 individual hospital units will be randomized to 3 groups (~19 units per group): 1) no change in signs; 2) changing signs monthly; and 3) changing signs weekly. To improve power, we will use stratified randomization with matching based on baseline hand hygiene compliance rates during Months 1-6. Block randomization will be used to ensure that baseline compliance rates will be evenly distributed across conditions. To do this, we will rank the units by compliance rate and then randomize by blocks of three using a computer-generated list of random numbers prepared by the Data Manager in consultation with the biostatistician. During Phase 3, the sign change strategy that was associated with the highest hand hygiene compliance will be universally implemented in the 59 study units in all 10 hospitals, this will set a new baseline and serve as a wash-out period. In our current study of hand hygiene interventions, we were able to detect a difference within six weeks. Thus, 3 months is likely enough time for wash-out.

Phase 4 will compare the additional benefits of the other 2 interventions—distribution of individual hand sanitizers to healthcare workers and obtaining cultures of healthcare workers' hands with visual feedback on hand contamination. In Phase 4, hospitals will be randomized to 3 groups: 1) signage only (4 hospitals); 2) signage and hand sanitizers (3 hospitals); and 3) signage and hand cultures (3 hospitals). Group assignment will again be stratified using block randomization (4, 3, 3), based on hand hygiene compliance rates measured during Phase 3. Individual strategies will be randomized by hospital to decrease contamination between wards/units. During Phase 5, the Phase 4 intervention associated with the highest compliance rates will be universally implemented; if both interventions were equally efficacious, the signage only hospitals will be randomized to receive either the hand sanitizer or hand culture intervention. Phase 5, like phase 3 will also serve as a washout period. Phase 6 will determine the potential incremental benefits of all 3 interventions in combination by re-randomizing

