## **8.0 Communication Plan**

All local sites will be engaged in research. All local sites will complete appropriate documentation to obtain approval of Central IRB with the help of the Iowa City study staff. Study coordinators from all sites will participate in weekly or bi-weekly conference calls in order to stay informed of changes to protocol. These meetings will also serve to update local sites about the event of any Serious Adverse Events, Unanticipated problems, or interim results that may impact the conduct of the study.

In addition to meetings in which we discuss study procedures, site visits by Iowa City study staff will occur at certain intervals during the study, at which time adherence to IRB-approved protocol will be verified.

When the study reaches a point at which a local site is no longer needed to be engaged in research, the Iowa City study staff coordinator will notify local facility directors and local site investigators by telephone.

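### On the natural reading, the covert observer also documents sanitizer distribution, in Phase 4 only in the three sanitizer hospitals; separately, observers in all arms may hear interim results

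*Protocol*

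**What the plan says.** **Who observes.** Section 4.0 (Resources and Personnel) lists the tasks of the nine sites other than Iowa City. The first is "conducting observations of potential HCW hand hygiene opportunities (Site Research Coordinator"). The other three, which are hanging signs, arranging sanitizer distribution and obtaining and displaying hand cultures, go to the Site PI/Hospital Epidemiologist.

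**What the measurement relies on.** Section 5.1, Operationalization of Primary Outcome, gives observers a cover story (severity-of-illness data in ICUs, a patient-movement survey on wards). On that basis it states that "the HCWs will not know they are being watched for infection control purposes, so they will not artificially increase their compliance". The safeguard stated for the observers themselves is training: "Observers will be research staff specifically trained and validated in hand hygiene observations". Nothing is said about masking them to allocation or keeping them away from intervention tasks.

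**Sanitizer.** Section 5.1, Distribution of Individual Hand Sanitizer Gel to HCWs, says "The Site PI/Hospital Epidemiologist will coordinate distribution with the Nurse Managers and Medical Directors overseeing the units". The next sentence says "The Research Coordinator will document how the hand sanitizers were distributed at each facility and provide the documentation to the Iowa City Research Coordinator". The observation form also records the source of the sanitizer used and "whether the individual hand sanitizer is visibly present on the HCW".

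**Calls.** Section 8.0 (Communication Plan) says "Study coordinators from all sites will participate in weekly or bi-weekly conference calls in order to stay informed of changes to protocol". It adds that these meetings will update sites on serious adverse events, unanticipated problems, or interim results that could affect how the study is run.

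**The concern.** The primary outcome is direct observation by someone who is supposed to be on the unit for an unrelated reason. The protocol devotes space to why this matters: it criticises programmes that do not conceal observation and links that practice to inflated rates. A covert observer should therefore hold no visible hand-hygiene role on the same units.

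Section 4.0 separates the two roles cleanly. The sanitizer text undoes that separation for one intervention only. If the documentation task makes the coordinator recognisable as part of the hand-hygiene study, the resulting reactivity would fall in one randomised arm and would favour it. Study Procedure in section 5.1 carries the Phase 4 intervention with the highest compliance into Phase 5, and the rule states no numerical margin, so a shift in one arm could bear on which add-on is chosen.

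The calls raise a different issue that is common to all arms: people who score the outcome may be told how the arms are doing while they are still scoring.

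**Working it through.** The protocol gives no figure on this point to reproduce. The check sets the assignments side by side and then asks what a shift would do.

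**1. Who does what (protocol)**

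| Task | Assigned to | Place |
|---|---|---|
| Covert observation | Site Research Coordinator (nine sites) | 4.0 |
| Hanging signs | Site PI/Hospital Epidemiologist | 4.0; 5.1, signs |
| Hand cultures | Hospital Epidemiologist or designated infection control staff | 5.1, hand cultures |
| Arranging sanitizer distribution | Site PI/Hospital Epidemiologist | 4.0; 5.1, sanitizer |
| Documenting sanitizer distribution | Research Coordinator, who reports to the Iowa City Research Coordinator | 5.1, sanitizer |

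The documenting sentence names the Iowa City coordinator separately as recipient, so the person documenting is most naturally the site's own coordinator. Sanitizer is then the only intervention that gives the observer a stated task.

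**2. Which arms are touched**

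- *Phase 4:* 4 hospitals signage only, 3 signage plus sanitizer, 3 signage plus cultures. Bottles go to the intervention hospitals, so the task arises in 3 of 10 hospitals, all in one arm.
- *Phase 6, if cultures won Phase 4:* sanitizer is new only in the 5 all-three hospitals, so the task is arm-specific again.
- *Phase 6, if sanitizer won Phase 4:* all 10 hospitals already have it from Phase 5, so the problem is no longer confined to one arm.
- *Calls:* coordinators from all sites attend, so this exposure is not arm-specific in any phase.

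**3. What a shift would do (illustration only)**

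Suppose there is no true effect and reactivity adds *b* points in the sanitizer hospitals. The estimated difference moves by *b*, whatever the clustering. The chance of a false-positive test depends on the variance used.

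- Inputs from section 5.6: 10 observations/hour × 60 hours/month × 6 months = 3,600 per hospital. Signage only: 4 × 3,600 = 14,400. Sanitizer: 3 × 3,600 = 10,800. Phase 4 baseline 65%.
- Assumptions: two-sided alpha 0.05; *b* = 2 points; intraclass correlation 0.005 to 0.05. The protocol states none of these.
- Independent observations: SE = √(0.65×0.35/14,400 + 0.67×0.33/10,800) = 0.0060; z = 0.02/0.0060 = 3.3; rejection probability about 91%.
- Clustered: design effect = 1 + 3,599 × ICC, which is 19.0 at ICC 0.005 and 181 at ICC 0.05. The rejection probability falls to about 12% and 6%.

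Under realistic clustering, then, the main exposure is the shift in the point estimate and hence in the choice of the highest arm, more than a spurious significant test. Nothing in the documents says whether *b* is 2 points, more, less or zero.

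**The case against.** **Contact with ward staff is not stated.** The documentation is made at facility level. The Site PI arranges distribution with unit managers, and the coordinator could complete the record from the Site PI without going near the units. A reader might infer that the cover story fails in the sanitizer hospitals. The documents do not support that; they support only that it is put at risk, because contact is not ruled out. This part of the objection stands.

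**The two roles may not be one person.** Section 4.0 names the observer by title for nine sites only, and section 5.1 speaks of research staff in the plural. The dual role is the natural reading, not an explicit statement. This also stands.

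**Observer neutrality is not a sanitizer-arm matter.** Interim results on calls would reach every site, and the wording is conditional. The roll-outs in Phases 3 and 5 generally reveal the winning arm anyway. Observers also see bottles, because the form requires it. A reader might infer that loss of neutrality is concentrated in the sanitizer hospitals; it is not. What remains is avoidable exposure to comparative results during a phase.

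**Size.** A reader might take the gap in section 2.0 between programme-reported compliance (87.2%) and rigorous observation (32.9% entry, 50.8% exit) and work out what share of recognised observations would produce the 5-point design effect. The documents do not support this. They give three causes for that gap and credit the Hawthorne effect only in part. The Phase 4 baseline assumed in section 5.6 is 65%, which leaves 87.2 − 65 = 22.2 points and not 36.4 or 54.3. No figure links recognition to a documentation form.

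**Safeguards exist.** Observers are trained and validated, stay for 10 minutes, and score room entry and exit, which the protocol calls the most reliably measured moments. These limit scoring drift. They do not address an observer who is recognised.

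**Conclusion.** The point holds as a risk created by the protocol's own assignments, not as a demonstrated failure. It has two separate parts.

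1. In Phase 4, the natural reading gives the covert observer an intervention-documentation task in the three sanitizer hospitals and nowhere else. If that leads to contact with ward staff, any reactivity would be differential and would favour the arm that may then be carried forward. This rests on reading the Research Coordinator as the site observer and on contact actually occurring.
2. In all arms, observers may hear interim compliance results while still scoring the outcome, because section 8.0 does not exclude them.

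Neither effect can be sized from the documents. The point deserves action because the remedy is cheap and removes an avoidable source of differential measurement. It does not show that the design is defeated.

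**What to change.** - **Section 5.1, sanitizer:** assign documentation of distribution to the Site PI/Hospital Epidemiologist, who already coordinates it, or to another person who does not observe.
- **Section 5.1, Operationalization of Primary Outcome:** state that observers take no part in delivering or documenting signs, sanitizer or cultures beyond what the observation form records.
- **Section 8.0:** keep observers out of call items that cover interim compliance results. They can attend the items on observation procedures and protocol changes.

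**Cost:** wording changes and a split call agenda, with no new staff. The Site PI takes on a short form per distribution round and documents their own distribution, which is a small loss of independence in the process record. The change will not mask observers fully, since they will still see bottles and will usually learn the winning strategy at each roll-out.
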